## Abstract

**Introduction:**

Medication-related problems (MRPs) are common among older adults. The global population is ageing and there are health-related challenges linked to ageing in rural areas. Home-living rural older adults often face barriers to access healthcare, like long distances to healthcare services and poor continuity of care. Telepharmacy is the remote provision of pharmaceutical care, and telepharmacy could be of particular importance for rural older adults to improve their access to clinical pharmacy services and reduce the incidence of MRPs. The objective of this study is to develop and evaluate a novel telepharmacy service in primary care for home-living older adults in Northern Sweden’s rural areas. The primary objective is to evaluate the effect of the telepharmacy service regarding the identification, classification and resolution of MRPs.

**Methods and analysis:**

This study will be conducted as a single-arm interventional study. A total of 100 people ≥65 years will receive the telepharmacy service for 12 weeks. The key principles of the telepharmacy service are to perform medication interviews and follow-up meetings with study participants, to conduct structured medication reviews, to conduct regular electronic medical record reviews and to have interprofessional collaboration with primary care physicians. All meetings will be conducted through video conferencing via a secure virtual care platform. Identified MRPs will be classified, and the acceptance rate of the pharmacists’ recommendations will be evaluated. The results will be presented with descriptive statistics. As secondary objectives, intra-individual changes in participants’ medication adherence, health-related quality of life and beliefs about medicines will be assessed through self-report questionnaires. Statistical analysis will be conducted using two-sided McNemar’s tests. Semi-structured interviews will also be conducted to explore participants’ and healthcare professionals’ experiences and attitudes towards this telepharmacy service.

**Ethics and dissemination:**

This study has been granted ethical approval by the Swedish Ethical Review Authority (registration number 2022-03819-01 and 2024-08441-02). Participant informed consent is required. The results will be published in peer-reviewed journals and presented at scientific conferences.

**Trial registration number:**

NCT05629936.

STRENGTHS AND LIMITATIONS OF THIS STUDYIntroduces and evaluates a novel telepharmacy service with video-based meetings for home-living older adults in Northern Sweden’s rural areas.The feasibility of the study design was qualitatively evaluated through individual interviews prior to finalisation of this study protocol.The absence of a control group hinders between-group comparisons.

## Introduction

 Multimorbidity and polypharmacy are common among older adults, and older people are at high risk of medication-related problems (MRPs).^1^,^3^ An MRP is defined as an event or circumstance involving medication therapy that actually or potentially interferes with desired health outcomes.^4^ Unidentified and unresolved MRPs can lead to unplanned hospital admissions^5 6^ and readmissions,^7^ increased healthcare costs^8^ and poor health-related quality of life.^9^

Additional health-related challenges are associated with ageing in rural areas and sparsely populated regions (SPRs). Home-living rural older adults often face several barriers to access healthcare, such as long distances to healthcare services, poor continuity of care and insufficient public transportation services.^10^,^14^ The Swedish Agency for Economic and Regional Growth (Tillväxtverket) classifies rural and urban areas based on geocoded statistics using 1×1 km grid squares.^15^ A grid square is considered dense if it has ≥300 people per km^2^. It is considered rural with <300 people per km^2^. If ≥5000 people are living in a cluster of neighbouring dense grid squares, the area is considered urban. If the total population in the cluster is <5000 the area is still considered rural, even if some grid squares are dense. The population density in Sweden is 25.8 inhabitants per km^2^ (in 2024), which, seen from a European perspective, is considered a relatively sparsely populated country.^16^ Västerbotten County, in Northern Sweden, has 5.1 inhabitants per km^2^. Several municipalities in Västerbotten County have a population density of less than one inhabitant per km^2^, which counts as a SPR according to research.^17^ Furthermore, the population in Västerbotten is ageing. This is a global phenomenon, which means that the whole world is facing this demographic challenge.^18^,^20^ There are several municipalities in Sweden, especially in the inland of Västerbotten County, where almost every third inhabitant is ≥65 years (in 2024).^21^

In recent years, telehealth has emerged as a promising complement to in-person care visits, and as a successful strategy to improve patients’ access to healthcare.^22^ Telehealth is defined as the use of telecommunication technologies to provide healthcare services where patients and providers are separated by distance.^23^ Telepharmacy is a subdivision of telehealth and is defined as the remote provision of pharmaceutical care via telecommunication technologies.^24^

There is a growing body of literature that highlights the use of telepharmacy to support the remote provision of clinical pharmacy services.^25 26^ Different telecommunication technologies have been used, such as video conferencing, telephone-based interventions and web-based applications. For instance, pharmacist-delivered telephone consultations and video conferencing have previously shown promising results regarding the provision of medication optimisation and disease management services in a geriatric primary care setting^27^ and in rural areas in the US.^28 29^ In addition, telepharmacy was also effectively used during the COVID-19 pandemic to perform remote medication reviews and to assess patients’ medication adherence.^26^

To our knowledge, there have been limited attempts to use telepharmacy services in primary care for home-living older adults in Northern Sweden’s rural areas. Telepharmacy could be of particular importance for rural older adults to improve their access to clinical pharmacy services and potentially reduce the incidence of MRPs. The objective of this study is therefore to develop and evaluate a novel telepharmacy service in primary care for home-living older adults in Northern Sweden’s rural areas. This telepharmacy service will be provided through video conferencing, and the primary objective is to evaluate the effect of the service regarding the identification, classification and resolution of MRPs. Secondary objectives are to compare participants’ medication adherence, health-related quality of life and beliefs about medicines through self-report questionnaires, between baseline and the end of the study. In addition, semi-structured interviews will be conducted to collect qualitative data about participants’ and healthcare professionals’ experiences and attitudes towards this telepharmacy service.

## Methods and analysis

This study protocol was developed in accordance with the Standard Protocol Items: Recommendations for Interventional Trials 2025 statement.^30^

### Principal study design

This study will be conducted as a single-arm interventional study. Home-living older adults in Northern Sweden’s rural areas will receive a telepharmacy service in primary care for 12 weeks.

### Study setting

This study will be conducted in collaboration with primary healthcare centres situated in Northern Sweden’s rural areas. A complete list of study sites is available at *clinical.trials.gov* (ID: NCT05629936).

The study will primarily be conducted in collaboration with primary healthcare centres in rural municipalities in Västerbotten County in Northern Sweden, potentially extending to neighbouring counties such as Västernorrland and Norrbotten if needed to gather enough participants. Additional healthcare centres will be invited to participate until the desired sample size of one hundred participants is reached.

The Swedish Agency for Economic and Regional Growth’s^15^ classification of rural municipalities will be used in this study. The agency divides rural municipalities into three subgroups: rural municipalities near urban areas, sparse rural municipalities and very sparse rural municipalities. In rural municipalities near urban areas, >50% of the population lives in rural areas, and most of the population is <45 min away by car to an urban area with at least 50 000 inhabitants. In sparse rural municipalities, >50% of the population lives in rural areas, and most of the population is more than 45 min away by car to an urban area with at least 50 000 inhabitants. In very sparse rural municipalities, the entire population lives in rural areas, and the entire population is more than 90 min away by car to an urban area with at least 50 000 inhabitants.

### Study population and recruitment

#### Eligibility criteria

People will be eligible for inclusion if they are (1) ≥65 years, (2) Living at home (ie, not in a nursing home), (3) Registered at primary healthcare centres in rural municipalities within Västerbotten County (and neighbouring counties if necessary) and (4) Using five or more prescribed medications and/or considered as a potential candidate by the primary care physician (PCP). An example of a potential candidate would be a person with multimorbidity, where a structured medication review could potentially improve patient’s medication-related outcomes. According to national regulations, people ≥75 years with at least five prescribed medications are entitled to receive a medication review once a year in primary care.^31^ In the present study, people aged 65 years or older will be included, as people ≥65 years are defined as older people, according to the statistical office of the European Union (Eurostat).^32^ People will be excluded if they are (1) Unable to communicate, (2) Do not speak Swedish, (3) Have a confirmed major neurocognitive disorder or (4) Receive palliative care.

#### Recruitment of study participants

The PCPs will use their patient lists to identify eligible participants. Eligible patients will be sent an invitation to participate, together with written information about the study, and a consent form (online supplemental material 1 (in Swedish)). They will also receive three different questionnaires about medication adherence,^33^ health-related quality of life^34^ and beliefs about medicines.^35^ All documents will be sent by mail to the patient’s home address. People who wish to participate sign the consent form, answer the questionnaires and return the documents by mail to the primary healthcare centre in a prepaid envelope provided by the research group. Through the consent form, the participant permits access to their contact details and electronic medical records. After receiving the signed consent form, a clinical pharmacist in the research group will contact the participant by phone. The participant will receive oral information about the study, and the clinical pharmacist and the participant will schedule an appointment for a video-based medication interview.

### Sample size

The aim is to include 100 participants. This sample size serves the dual purpose of describing the prevalence of MRPs within the study population with good precision and enabling the statistical evaluation of changes in key outcome measures (eg, self-reported medication adherence, measured dichotomously) from baseline to the end of the study through intra-individual comparisons. No comparison group is included.

A priori power calculation has been performed to size the study with respect to the intra-individual comparison of the proportion of adherent participants. Based on the assumptions of a clinically relevant increase in the proportion of adherent participants from 85% at baseline to 95% at the end of the study (ie, an absolute difference of 10 percentage points), and an expected correlation (phi coefficient) of 0.6 between the two measurement time points, 80 participants are required to achieve 80% statistical power to detect this difference using a two-sided McNemar’s test at a 5% significance level (α=0.05), with continuity correction applied. The assumptions about the proportions of adherent participants are based on results from previous studies on self-reported medication adherence using the Medication Adherence Report Scale (MARS-5) questionnaire.^36 37^

Since the planned inclusion is 100 participants, which exceeds the calculated requirement of 80, the study will have >80% power to identify a difference of this magnitude under the given assumptions. The sample size also accounts for a potential dropout rate of 20%. The sample size of 100 participants is therefore considered well-justified and adequate to meet the study’s descriptive aims and allow for meaningful analyses of changes over time.

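### The assumed phi of 0.6 cannot occur with 85% and 95% adherence (maximum 0.546), so the stated requirement of 80 participants comes from an impossible table

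*Protocol article*

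**What the plan says.** The Sample size section of the protocol article gives the study two purposes: a precise description of medication-related problems and a within-person test of change in outcomes such as adherence. Only the second is quantified. The inputs are an "increase in the proportion of adherent participants from 85% at baseline to 95% at the end of the study", "an expected correlation (phi coefficient) of 0.6 between the two measurement time points", and a "two-sided McNemar’s test at a 5% significance level (α=0.05), with continuity correction applied". From these the section states that "80 participants are required to achieve 80% statistical power to detect this difference".

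It then says "The aim is to include 100 participants", claims more than 80% power because 100 exceeds 80, and adds: "The sample size also accounts for a potential dropout rate of 20" per cent. The planning case after dropout is therefore 100 × 0.8 = 80 evaluable pairs.

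**The concern.** For paired yes/no data, the two marginal proportions limit how strongly the measurements can be correlated. Anyone adherent at both times was adherent at baseline, so the both-adherent cell cannot exceed 85%. That caps phi below 0.6. If the cap is ignored, the sample-size formula still returns a number, but it is too small, because a higher phi means fewer discordant pairs and a smaller n.

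At stake is the only numerical justification of the trial size. If the adherence comparison turns out non-significant, readers will judge that result against 80% power, which the study may not have.

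**Working it through.** **Inputs** (all from the Sample size section): p1 = 0.85, p2 = 0.95, d = 0.10, phi = 0.6, two-sided α = 0.05 (z = 1.96), power 80% (z = 0.8416), continuity correction, planned inclusion 100, dropout 20%.

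**1. Cells implied by phi = 0.6**

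- s = √(0.85 × 0.15 × 0.95 × 0.05) = 0.07782
- Both adherent: 0.85 × 0.95 + 0.6 × 0.07782 = 0.8075 + 0.0467 = 0.8542, above the 0.85 baseline margin
- Adherent to non-adherent: 0.85 − 0.8542 = −0.0042
- Non-adherent to adherent: 0.95 − 0.8542 = 0.0958
- Total discordance ψ = 0.0916, smaller than the net change of 0.10, which is impossible

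**2. Largest feasible phi**

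phi_max = (0.85 − 0.8075) / 0.07782 = 0.546. At this value nobody moves from adherent to non-adherent.

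**3. Reproducing the stated 80**

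- Uncorrected: n = [1.96√ψ + 0.8416√(ψ − d²)]² / d². With ψ = 0.0916, n = 69.5.
- Continuity-corrected: (n/4) × [1 + √(1 + 2/(n d))]² = (69.5/4) × [1 + √(1 + 2/6.95)]² = 79.2, rounded up to 80.

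The stated figure is matched with the impossible table as input.

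**4. Feasible values**

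The n column uses the same corrected formula. Power is by exact enumeration of the continuity-corrected test: a binomial number of discordant pairs, then a binomial split between directions. Phi values below 0.546 are assumptions shown as a range, since the protocol gives no other value.

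| phi | improve | deteriorate | n by formula | power, 80 pairs | power, 100 pairs |
|---|---|---|---|---|---|
| 0.546 | 10.0% | 0% | 86 | 82% | 94% |
| 0.5 | 10.4% | 0.4% | 92 | 77% | 90% |
| 0.4 | 11.1% | 1.1% | 104 | 68% | 81% |
| 0.3 | 11.9% | 1.9% | 116 | 61% | 73% |

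**5. Where 80 pairs reach 80% power**

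Enumerated power with 80 pairs is 81.6% at phi 0.54 and 80.5% at 0.53, and it crosses 80% just above 0.525. At 0.525 the deteriorating proportion is 0.85 − (0.8075 + 0.525 × 0.07782) = 0.0016, or about 0.16%.

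**6. Formula against enumeration**

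The formula is somewhat conservative. By enumeration the smallest n for 80% power is 78 at the feasible maximum (formula 86) and 98 at phi 0.4 (formula 104).

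**The case against.** The strongest defence is that little changes in practice. At the feasible phi closest to the stated one, enumeration needs only 78 pairs, so 80 would be enough there. The plan enrols 100, and with all of them evaluable power stays above 80% down to phi of about 0.4. The lower power figures depend on phi values that the protocol does not give. Adherence is a secondary objective, and medication-related problems, the primary outcome, are analysed descriptively.

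All of this stands, and it limits the point. It does not rescue the stated assumption, since no population has these margins with phi 0.6. Nor does the adequacy of 80 pairs near the maximum support the published reasoning: that result needs almost no one to deteriorate, which the protocol neither states nor defends. The claim of more than 80% power and the allowance for 20% dropout hold together only in that narrow band.

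Two stronger readings are tempting but unsupported. A reader might infer that 80 pairs reach 80% power only if nobody at all deteriorates; enumeration shows a narrow band from just above 0.525 to 0.546. A reader might also infer that the trial is too small and must enrol more. Keeping 80% power after 20% dropout at phi 0.4 would take about 98/0.8 = 123 to 104/0.8 = 130 enrolled, but the protocol gives no basis for 0.4 over another feasible value, and adherence is not the primary outcome.

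**Conclusion.** The calculation is wrong as written. That phi 0.6 is impossible, and that the corrected formula gives at least 86 instead of 80, follows from the protocol's own numbers without any outside assumption. How far power falls does depend on an assumption. With 80 evaluable pairs it is at least 80% only if at most about 0.16% of participants deteriorate, and it is 77%, 68% and 61% at phi 0.5, 0.4 and 0.3. With 100 evaluable pairs, power above 80% holds for phi of about 0.4 or more, so only if there is no dropout. These figures take the 85% and 95% margins and the continuity-corrected test as given.

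The error concerns the power statement for a secondary outcome. It does not touch the primary descriptive analysis.

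**What to change.** In the Sample size section:

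- Replace phi 0.6 by a feasible value (at most 0.546) that the investigators justify, and state the proportions improving and deteriorating that it implies.
- Restate the required number of evaluable pairs, saying whether it comes from the formula or from exact enumeration.
- Give power at both 100 and 80 evaluable pairs over a range of phi. As an illustration only, phi 0.4 means 11.1% improve and 1.1% deteriorate, and needs about 98 (enumeration) to 104 (formula) evaluable pairs for 80% power.
- Keep enrolment at 100, and say plainly that power for the adherence comparison may be below 80% after 20% dropout.

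The cost is one rewritten paragraph and a less favourable power statement. Trial conduct and the primary analysis do not change.

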### Telepharmacy service

The key principles of this telepharmacy service (figure 1) are to perform medication interviews and follow-up meetings with study participants, to conduct structured medication reviews, to conduct regular electronic medical record reviews and to have interprofessional collaboration with PCPs. All meetings will be conducted through video conferencing via Visiba Care,^38^ which is a secure virtual care platform. It is used for remote healthcare consultations by several healthcare providers, among others Region Västerbotten. The participants will be able to attend the meetings from home through their own electronic devices such as computers, phones or tablets. The meetings will not be recorded.

**Figure 1 F1:**
[figure not shown]
Flowchart of the telepharmacy service.

All clinical pharmacists performing the intervention will hold a degree of Master of Science in Pharmacy or equivalent qualifications. They should have been previously trained to conduct structured medication reviews or hold relevant education in clinical pharmacy.

This telepharmacy service will be a complementary service to the participants’ regular care. In the case of incidental findings, these findings will be communicated to the participant’s PCP, who either handles the case themselves, or forwards it to the appropriate healthcare unit. Furthermore, the participants will be covered by the ordinary insurance cover for patients within Swedish primary care.

#### Video-based medication interview with study participant

Initially, the clinical pharmacist schedules a meeting for a video-based medication interview with the participant. During the meeting, the clinical pharmacist conducts a medication reconciliation to obtain a complete and accurate list of the participant’s current medications. The pharmacist also asks questions about the participant’s medication management, medication adherence, drug allergies, the use of over-the-counter (OTC) medications, dietary supplements and herbal medicines. The clinical pharmacist can also respond to participants’ medication-related questions. During the meeting, the clinical pharmacist also assesses if the participant experiences symptoms that may be related to their medication therapy, by using the Swedish version of the PHArmacotherapeutical Symptom Evaluation-20 questions (PHASE-20) tool.^39^ PHASE-20 is a validated assessment tool that is frequently used in medication reviews to identify symptoms that may be caused by the patient’s medication therapy. The tool is comprised of 19 symptoms or sets of symptoms that are considered common regarding adverse drug effects in older adults. The tool also contains an open question, if the respondent wishes to address additional symptoms than the pre-formulated ones.

#### Structured medication review and video-based interdisciplinary meeting with the primary care physician

Shortly after the medication interview, the clinical pharmacist conducts a structured medication review (table 1) based on information from the interview and the participant’s electronic medical records. Potential MRPs that cannot be resolved through direct contact with the participant are presented and discussed with the PCP during a pre-scheduled meeting in Visiba Care. During this interdisciplinary meeting, the clinical pharmacist presents recommendations to resolve potential MRPs, and the PCP may accept or reject the pharmacist’s recommendations. The PCP then informs the participant about any changes in their medication therapy and follows up and monitors these changes.

**Table 1 T1:** Structured medication review principles

Medication reconciliation	Identify an accurate list of current medications according to the participant’s statements and electronic medical records
Current health conditions and diseases	Are there valid medical indications for all medications in the medication list? Any untreated conditions?
Overall review of current medication treatments	Check for desired therapeutic effects. Determine if the choice of medications, doses, dosing intervals and treatment durations is appropriate according to current clinical guidelines and recommendations
Side effects, contraindications and inappropriate medications	Check for possible side effects or adverse events. Check for improper drug selections or contraindications, for example, due to certain medical conditions or impaired body functions such as reduced renal or hepatic function
Clinically relevant interactions	Check for drug-drug interactions and food-drug interactions
Medication adherence	Assess whether the participants take their medications as prescribed. Medication non-adherence can be intentional (deciding not to follow the treatment regimen) or unintentional (eg, due to a misunderstanding of treatment instructions or being unable to pay for the medication)
Practical aspects of medication administration	Assess whether the participant has swallowing difficulties or problems with opening medication containers. Are suitable/preferred dosage forms being used? Are medical information and dosing instructions clear and well understood?
Cost-effectiveness	Check for cost-effective use of medications that follow current recommendations. Is the current treatment cost-effective, or are there therapeutically equivalent options available at a lower cost?

